### 4.2 Inclusion criteria

In order to be eligible to participate in this study, a subject must meet all of the following criteria:

- Age 18-85 years (extremes included), males and females.
- Body mass index (BMI) between 19.0 and 30.0 kg/m^2, inclusive
- General good health, without significant medical illness, as determined via physical exam findings, or vital signs
- No clinically significant laboratory abnormalities as determined by the investigator
  - o Note: one retest of lab tests is allowed within the screening window
- Informed Consent Form signed voluntarily before any study-related procedure is performed, indicating that the subject understands the purpose and procedures required for the study and is willing to participate in the study
- Willing to adhere to the prohibitions and restrictions specified in this protocol
- All participants have received a completed (registered) vaccine at least 3 months before inclusion in this study (i.e. Pfizer [Comirnaty], Moderna [Spikevax], Janssen [Ad26.COV2.S], AstraZeneca [Vaxzevria]).
- Negative hepatitis panel (including hepatitis B surface Ag and anti-hepatitis C virus Abs) and negative human immunodeficiency virus Ab and Ag screens at screening
- Female subjects should fulfil one of the following criteria:
  - o At least 1 year post-menopausal (amenorrhea >12 months)
  - o Surgically sterile (bilateral oophorectomy, hysterectomy, or tubal ligation);
  - o Will use adequate forms of contraceptives from screening to discharge.
- Female subjects of childbearing potential and male subjects who are sexually active with a female partner of childbearing potential must agree to the use of an effective method of birth control from screening to discharge
  - o Note: medically acceptable methods of contraception that may be used by the subject and/or partner include combined oral contraceptive, contraceptive vaginal ring, contraceptive injection, intrauterine device, etonogestrel implant, double barrier, sterilization and vasectomy
- Female subject has a negative pregnancy test at screening and upon check-in at the clinical site.
  - o Note: pregnancy testing will consist of a serum pregnancy test at screening and urine pregnancy tests at the dosing visit, in all women.

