#### 4.4 Sample size calculation

The study consists of a Phase II clinical study. The following stopping-rule will be applied on a cohort-by-cohort basis: for a particular cohort, any SAE or AE  $\geq 3$  (according to NCI Common Terminology Criteria for Adverse Events [CTCAE]) attributable to AKS-452X.

On the basis of the phase I/II safety assessment data conducted and a minimum project enhanced immune response rate of 80% for each cohort.

Enhanced immune response rate is defined as:

- i) Seroconversion based on a true positive based on the SP/RBD IgG ELISA assay positive/negative cutoff criteria using the quantitative cut-off value defined by the assay kit batch expressed in  $\mu\text{g/mL}$ . The positive/negative cutoff value was established as 2.42  $\mu\text{g/mL}$  from the validation analysis for the current lot of assay kits, but it should be noted that for each new lot of assay kits, Akston QC performs a re-validation of the cutoff value in order to maintain clinical agreement from lot-to-lot, and/or
- ii) Two times (2x) the baseline SP/RBD IgG at day 28 after boosting, as compared to the titer just before vaccination (day 0).

Based on the observed seroconversion rates in phase I/II and the statistical assessment for the phase II ACT-BOOSTER, a total study group of 150 subjects per cohort of registered vaccine (i.e. Pfizer [Comirnaty], Moderna [Spikevax], Janssen [Ad26.COV2.S], AstraZeneca [Vaxzevria]), totalling 600 subjects is regarded statistically significant to confirm the hypothesis. The statistical assessment providing the above stated numbers is based on the following argumentation (see Table 2 and Figure 9).

| Fixed Scenario Elements |                      |
|-------------------------|----------------------|
| Method                  | Normal approximation |
| Number of Sides         | U                    |
| Null Proportion         | 0.7                  |
| Nominal Power           | 0.8                  |
| Variance Estimate       | Null Variance        |
| Alpha                   | 0.05                 |

| Computed N Total |            |              |         |
|------------------|------------|--------------|---------|
| Index            | Proportion | Actual Power | N Total |
| 1                | 0.80       | 0.800        | 119     |
| 2                | 0.82       | 0.802        | 81      |
| 3                | 0.84       | 0.803        | 58      |
| 4                | 0.86       | 0.803        | 43      |

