## 7. METHODS

### 7.1 Study parameters/endpoints

#### 7.1.1 Main study parameter/endpoint

**Main study parameters/endpoints: Primary endpoint:** The percentage of patients that i) achieve an SP/RBD-specific IgG antibody titer level of  $\geq 2.42 \mu\text{g/mL}$  at the day 28 time-point post-intervention (i.e. booster vaccine) if the base-line value prior to receiving the booster vaccine was  $< 2.42 \mu\text{g/mL}$  or ii) where the SP/RBD-specific IgG antibody titer is at least 2x the base-line value prior to receiving the booster vaccine if the base-line value prior to receiving the booster vaccine was  $\geq 2.42 \mu\text{g/mL}$ . The percentage of patients in each of the four cohorts that achieve the primary endpoint threshold at 28 days post-intervention will be calculated (n (%)).

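### The enhanced immune response in Sections 4.4 and 7.7 is not the primary endpoint of 7.1.1: no baseline condition, different days, different cutoff rule

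*Protocol*

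**What the plan says.** **Primary endpoint (Summary, endpoint paragraph, and Section 7.1.1, same wording).** The two limbs exclude each other. With a baseline below 2.42 µg/mL, the subject must reach 2.42. Otherwise the titer must be "at least 2x the base-line value prior to receiving the booster vaccine if the base-line value prior to receiving the booster vaccine was" at or above 2.42. The closing sentence fixes the assessment at 28 days after the booster. The cutoff is a fixed number.

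**Section 4.4.** The sample size is built on "a minimum project enhanced immune response rate of 80% for each cohort". Limb (i) of that response is seroconversion, described as a true positive against the ELISA cutoff. Its text ends "Akston QC performs a re-validation of the cutoff value in order to maintain clinical agreement from lot-to-lot, and/or", and limb (ii) follows: a doubling at day 28 relative to day 0. Neither limb has a baseline condition. The cutoff is the value defined by the kit batch, currently 2.42 µg/mL and re-validated for each new lot.

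**Section 7.7.** Under a paragraph marked mandatory, each cohort must show at least 80%, with at least 119 subjects in the final analysis. The limbs and the *and/or* link match 4.4, but the doubling is read at day 56 against the titer at screening, with day 0 in brackets.

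**Summary, intervention paragraph.** It gives the same two limbs without a linking word, with the doubling at day 56 against the screening titer.

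**Population (Section 4.2).** "All participants have received a completed (registered) vaccine at least 3 months before inclusion in this study". Neither 4.2 nor 4.3 sets a limit on baseline titer.

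**The concern.** The protocol holds two responder rules that classify the same subject differently. The one with a number attached to it (80% for planning, 80% as a cohort requirement) is not the primary endpoint.

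The difference matters because everyone enrolled has already been vaccinated. If limb (i) is met by being positive after the booster, a subject who was positive before it and did not respond still counts. The cohort rate then mixes persistence of the first vaccine's antibody with the effect of the booster, and the requirement in 7.7 could be met without a booster effect. Two incompatible response rates could each be reported as defined by the protocol.

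**Working it through.** **1. The plan's own sample size reproduces.** Inputs from Section 4.4, Table 2: "Null Proportion | 0.7", "Number of Sides | U" (one-sided, upper), alpha 0.05, "Nominal Power | 0.8", "Variance Estimate | Null Variance", assumed rate 0.80.

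n = [(1.645·√(0.7·0.3) + 0.842·√(0.8·0.2)) / (0.80 − 0.70)]² = [(0.754 + 0.337)/0.10]² ≈ 118.9, so 119, as stated. The other seven rows of Table 2 reproduce as well. With 20% drop-out, 119/0.8 = 148.75, so 149; the plan rounds to 150. The arithmetic is sound. The question is which responder rule the 70% and 80% refer to.

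**2. The rules side by side.** Seroconversion can be read as a level (above the cutoff after the booster) or as a change (negative to positive).

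| Subject (µg/mL) | 7.1.1 | 4.4/7.7, level reading | 4.4/7.7, change reading |
|---|---|---|---|
| Baseline ≥2.42, stays positive, less than doubles | no | **yes** | no |
| Baseline ≥2.42, doubles | yes | yes | yes |
| Baseline <2.42, reaches 2.42 | yes | yes | yes |
| Baseline <2.42, doubles, stays below 2.42 (e.g. 0.8 to 1.8, a factor of 2.25) | no | **yes** | **yes** |

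Neither reading makes the rules agree. The level reading creates the large gap (row 1); the change reading leaves only row 4.

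**3. Day, reference and cutoff.**

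| Place | Doubling read at | Compared with | Cutoff |
|---|---|---|---|
| Summary endpoint, 7.1.1 | day 28 | value before booster | fixed 2.42 |
| 4.4 | day 28 | day 0 | per kit lot |
| 7.7 | day 56 | screening (day 0) | per kit lot |
| Summary, intervention | day 56 | screening | per kit lot |

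In the Section 7.3 schedule, screening is day −28 to −2, and blood for humoral response is first drawn on day 0. Screening and day 0 are therefore different visits, and no screening titer is scheduled.

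**4. What a booster with no effect would score.** Assumptions: level reading, stable titers, a share b of the cohort positive at baseline. The protocol does not give b, so a range is shown. The response rate under 4.4/7.7 is then about b.

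- The 80% requirement at n = 119: 0.80·119 = 95.2, so at least 96 responders.
- The Z test against 0.70: 0.70 + 1.645·√(0.21/119) = 0.769, and 0.769·119 = 91.5, so at least 92 responders (77.3%).

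Exact binomial tails, n = 119:

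| b | P(at least 96), the 80% requirement | P(at least 92), the Z test |
|---|---|---|
| 0.70 | 0.6% | 4.8% |
| 0.75 | 9% | 32% |
| 0.80 | 48% | 80% |
| 0.85 | 92% | 99.1% |
| 0.90 | 99.9% | >99.9% |

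**5. The same booster under 7.1.1.** Only assay noise produces responders. A simulation with assumed assay CV of 20–30%, log-scale SD of 1 between subjects and median baseline of 2.42 to 50 µg/mL gives about 1% to 8%. Under the change reading of 4.4/7.7 it gives about 1% to 10%. None of these comes near 70% or 80%.

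**The case against.** The strongest reply is that the designated primary endpoint is sound. It appears in the same words in the Summary and 7.1.1, depends on baseline, is fixed at day 28, and is the percentage that 7.1.1 says will be calculated. IgG is also measured at days 0, 28, 56, 91, 182 and 273. This stands. A reader might infer that the trial cannot say whether the booster raised antibody; the documents do not support that.

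Second, seroconversion ordinarily means negative to positive, and on that reading a booster with no effect does not pass. The legend to Figure 8 defines it as a level above 2.42 µg/mL, which favours the level reading. It does not settle the matter, because all Day 0 samples there were below the limit of quantification, so level and change coincide. The no-effect result is therefore conditional. The conflict between the rules is not, since row 4 of the comparison remains under either reading.

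Third, the baseline share is unknown. Section 4.2 sets only a minimum of 3 months since vaccination, and the Summary expects immunity not to be long-lived, so a share below 80% cannot be excluded. A reader might infer that the 80% requirement is nearly certain to be met. That holds only from about 85–90% positive at baseline; at 75% the chance is 9%.

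Fourth, the 80% sentence in 7.7 sits under premature termination and names no consequence. That is fair, but the paragraph is marked mandatory and is the only place where a cohort result is judged against a threshold.

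A reader might also infer that a change of kit lot between day 0 and day 28 would create false fold-rises. Nothing in the protocol says paired sera are read on different lots, and the stated purpose of re-validation is agreement between lots. Only the fixed versus per-lot cutoff is a discrepancy in the text.

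**Conclusion.** The inconsistency is real and needs no calculation: 4.4 and 7.7 do not define the endpoint of 7.1.1, and they disagree with it or with each other on baseline condition, day, reference titer and cutoff. Following 7.7 as written can give a wrong pass.

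The size of that risk rests on two assumptions: that seroconversion means a level, and the share positive at baseline. With stable titers and n = 119, the chance that a booster with no effect reaches 80% runs from 0.6% (70% positive) through 48% (80%) to 99.9% (90%). Under 7.1.1 it is negligible. The primary endpoint itself and the sample size arithmetic are not in question.

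**What to change.** - Replace the free-standing definitions in the Summary intervention paragraph, 4.4 and 7.7 with a reference to 7.1.1: baseline-conditional, day 28 against the pre-booster value on day 0.
- State that the 80% planning rate in 4.4 and the 80% criterion in 7.7 refer to that endpoint.
- State one cutoff rule in all places, either 2.42 µg/mL or the validated value of the kit lot used.

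The cost is protocol wording only. N stays at 119 evaluable and 150 enrolled per cohort. The downside is that the rate judged against 80% may be less favourable, because subjects who were already positive must double to count.

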## TREATMENT OF SUBJECTS

The subjects will receive an immunological treatment in the form of a vaccination.

### **4.5 Investigational product/treatment**

The investigational product is a fusion-protein based vaccine.

### **4.6 Use of co-intervention (if applicable)**

There are no-specific life-rules, diet or co-medication for the duration of the study when subjects participate.

### **4.7 Escape medication (if applicable)**

In case of an allergic reaction, the Standard Operating Procedure 'Anaphylactic Reaction' is activated and in summary consists of the following escape medication: anti-histamine medication (e.g. clemastatine 10 mg p.o., dexamethasone (4 mg p.o.) and in case of a severe reaction epinephrine, oxygen and alarm UMCG Emergency Crash Team at the ward.

## 5. INVESTIGATIONAL PRODUCT

### 5.1 Name and description of investigational product(s)

AKS-452 is a recombinant fusion protein comprising a portion of the SARS-CoV-2 SP/RBD and an Fc fragment containing a portion of the hinge, and the full CH2, and full CH3 domains of the human IgG1 Fc fragment that are connected via a covalent peptide linker sequence (**Figure 3**). The resulting SARS-CoV-2 SP/RBD-Fc fusion protein, when made in CHO cells, is expressed as the homodimer of two identical Fc fusion protein chains that are connected via multiple disulfide bonds. The homodimer is encoded by a single nucleic acid molecule, much in the same way that a monoclonal antibody heavy chain is encoded and expressed in CHO cells. Detailed information on the production of AKS-452 and the more concentrated version AKS-452X can be found in the IMPD, section 2.1.S Drug Substance and 2.1.P Drug Product

### 5.2 Summary of findings from non-clinical studies

A summary of findings from non-clinical studies can be found in the Investigators Brochure (IB) and Investigational Medicinal Product Dossier (IMPD), in:

- IB AKS-452 version 3.0 (2021-09-23), section 4
- IMPD AKS-452X (concentrated) version 3.0, section 2.2

### 5.3 Summary of findings from clinical studies

Summary of the DSMB report (07-08-2021): Trial representatives informed the DSMB about the progress of the study. Furthermore, we received all necessary and relevant study material for the DSMB meeting and reviewed and discussed the safety data after the first six cohorts of patients in this trial. The trial is accomplished as described in the approved research protocol. Monitoring of the project has been carried out correctly and does not give cause for extra concern. In all dosing cohorts, mild adverse events were mainly related to the injection site and subsided after days to weeks without residual effects. Other AEs were likely related to the vaccine. The DSMB concludes that the phase I study has not shown any safety concerns. Given this conclusion, the DSMB did not object to progressing to the phase II study with the proposed dose of 45 micrograms given twice or 90 micrograms given once subcutaneously.

### 5.4 Summary of known and potential risks and benefits

#### *Overall Conclusion for Phase I Data*

The overall safety assessment of AKS-452 in the ongoing phase I/II ACT clinical study in six cohorts totaling 60 participants in phase I and 52 in phase II, showed limited side-effects over all dosing-cohorts. No SAEs attributable to the vaccine were observed. Mild AEs due to the vaccine were observed, comparable to the current registered anti-COVID-19 vaccines. Moreover, no laboratory abnormalities were observed which were attributable to the vaccine. In all dosing cohorts, a  $\geq 70\%$  seroconversion rate was observed, whereas the results for each of the cohorts after a single dose were comparable to values measured from confirmed COVID-19 positive convalescent serum samples. 100% seroconversion was seen in the cohorts using 2x 45 µg, 1x 90 µg and 2x 90 µg.

**Anti-COVID19 Vaccination AKS-452X BOOSTER Study (Protocol nr. 901452-CT-21-001)**

The repeated dose toxicity study in New Zealand White Rabbits revealed that no significant mortality or organ weight changes were observed at the main study termination. Mild effects, such as increases in fibrinogen, were most likely due to the Montanide ISA 720 adjuvant during the Dosing Phase which subsided during the recovery phase. The expected macroscopic and microscopic transient redness of the injection site were also likely due to adjuvant. These findings from the animal toxicity studies on the adjuvant are in line with clinical findings of adverse events in clinical trials. A potential risk is an allergic reaction after the injection of AKS-452X. In this trial, to guard the subjects' safety during and after AKS-452X injection, they will be closely observed until 15 minutes post injection by qualified nurses, who will be ready to promptly intervene.

**5.5 Description and justification of route of administration and dosage**

In the underlying RP of the phase II AKS-452X ACT-BOOSTER trial, one booster dosage will be investigated in terms of enhanced immune response and secondary safety. Based on the preclinical trials in rabbits, non-human primates and clinical data we anticipate that one dose of 90 µg will generate sufficient seroconversion and/or immune enhancement to protect against SARS-CoV-2 infection after having received a registered vaccine  $\geq 3$  months ago. The route of administration for the human clinical setting is subcutaneous injection based on (pre-)clinical studies. The trial consists of four study arms of the four registered vaccines (**Figure 7**), of 150 subjects per cohort of registered vaccine (i.e. Pfizer [Comirnaty], Moderna [Spikevax], Janssen [Ad26.COVS.S], AstraZeneca [Vaxzevria]), totalling 600 subjects

**5.6 Dosages, dosage modifications and method of administration**

Naked AKS-452X (5x concentrated without Montanide ISA 720 adjuvant) will be mixed with sterile saline at a 1:4 ratio (v/v), and doses of 90 µg (with a total volume of 150 µL of the diluted AKS-452X solution) will be injected subcutaneously. For more details see 6.5.

**5.7 Preparation and labelling of Investigational Medicinal Product**

AKS-452X has been produced according to GMP standards. The final product has been verified by an identity method based on SEC-HPLC. The product has been filled in vials under GMP conditions to a final concentration of 3000 µg/mL in phosphate buffered saline (pH 7.2). The vials are stored frozen at -80°C, but are thawed on day of use. A copy of the primary and secondary label according to GMP standards is provided in the IMPD.

**5.8 Drug accountability**

The investigational agents are stored at the (co-)investigators pharmacy (Department of Clinical Pharmacy, University Medical Center Groningen, The Netherlands). If investigational agents would need to be shipped (for example after creating aliquots of the study compound by an external subcontractor), they will be shipped to the Principal Investigator's authorized designee, who will check and record the amount and condition of the agents received. All shipments of investigational agent will include an enclosed packing slip; the slip must be signed by the designee and returned to the shipper to verify receipt of investigational agent. At the end of the study or as directed, all used and unused supplies, including partially used or empty containers,

**Anti-COVID19 Vaccination AKS-452X BOOSTER Study (Protocol nr. 901452-CT-21-001)**

---

will be disposed of or transferred in accordance with local written procedures, if applicable. Any disposal or transfer of investigational agent shall be noted on the investigational drug disposition log and signed-off by a second person.

## **6. NON-INVESTIGATIONAL PRODUCT**

### **6.1 Name and description of non-investigational product(s)**

Not applicable

### **6.2 Summary of findings from non-clinical studies**

Not applicable

### **6.3 Summary of findings from clinical studies**

Not applicable

### **6.4 Summary of known and potential risks and benefits**

Not applicable

### **6.5 Description and justification of route of administration and dosage**

Not applicable

### **6.6 Dosages, dosage modifications and method of administration**

Not applicable

### **6.7 Preparation and labelling of Non-Investigational Medicinal Product**

Not applicable

### **6.8 Drug accountability**

Not applicable

## 7. METHODS

### 7.1 Study parameters/endpoints

#### 7.1.1 Main study parameter/endpoint

**Main study parameters/endpoints: Primary endpoint:** The percentage of patients that i) achieve an SP/RBD-specific IgG antibody titer level of  $\geq 2.42 \mu\text{g/mL}$  at the day 28 time-point post-intervention (i.e. booster vaccine) if the base-line value prior to receiving the booster vaccine was  $< 2.42 \mu\text{g/mL}$  or ii) where the SP/RBD-specific IgG antibody titer is at least 2x the base-line value prior to receiving the booster vaccine if the base-line value prior to receiving the booster vaccine was  $\geq 2.42 \mu\text{g/mL}$ . The percentage of patients in each of the four cohorts that achieve the primary endpoint threshold at 28 days post-intervention will be calculated (n (%)).

#### 7.1.2 Secondary study parameters/endpoints

Safety evaluation in the four cohorts for local and systemic adverse events after injection every pre-defined scheduled follow-up (post intervention. Patients will continue to be followed passively for additional safety events out to 9 months post-intervention.

To achieve these objectives, the following will be measured:

- Anti-SARS-CoV-2 SP RBD IgG titers at days 0, 28, 56, 91, 182 and 273 post-boostering.
- Serum titer inhibition of recombinant ACE2-SP/RBD binding and/or neutralization of live SARS-CoV-2 virus infection of live cells (Plaque Reduction Neutralization Test, PRNT) at days 0, 28, and 182
- T-cell responses measured ex vivo using PBMCs to measure SP/RBD-specific T cell production of IFN- $\gamma$  and Th1/Th2/Th17 related cytokines via ELISpot or other Ag-specific flowcytometric-based assays on days 0, 28, and 182.

